## **2.3 Research objectives**

Research objectives include:

### **Part 1 – Survey:**

Primary objectives:

- Understand the disease presentation (diagnoses, signs/symptoms, procedures) between the time of the first suspected symptom and date of diagnosis in patients with ATTRv or ATTRwt amyloidosis
- Evaluate healthcare provider interactions between first suspected symptom and date of diagnosis

Secondary objective:

- Evaluate the similarities and differences in the diagnostic journeys of ATTRwt and ATTRv amyloidosis patients

### **Part 2 – Interviews:**

- Gain an in-depth understanding of the overall disease burden and symptom development during the diagnostic journey from the patient's perspective, including the impact on quality of life (QOL), ability to work, relationships, and general health status
- Assess the key milestones, including interactions with healthcare providers and major disease worsening events, and the timeline of early disease progression from the patient perspective
- Evaluate the quality of the patients' interactions with the healthcare system during their diagnostic journey, assessing both drivers that assisted in making the diagnosis of ATTR amyloidosis, as well as unmet medical needs during this time

## **2.4 Study design**

### **2.4.1 Study background**

Part 1 of this study includes an observational, online, one-time survey was conducted between November 30–December 8, 2020, following ethics approval granted November 24, 2020.

This survey was completed by patients residing in the US with self-disclosed confirmed diagnosis of ATTRwt or ATTRv amyloidosis. The survey contained questions related to patient demographics, medical history (signs, symptoms, diagnoses, procedures related to neuropathic, orthopedic, or cardiac manifestations associated with ATTR amyloidosis and related physician specialty interactions), and the patient experience during the period prior to ATTR amyloidosis diagnosis.

The survey was developed in collaboration with patients from the Alnylam standing patient advisory board, the ASG leadership, clinical ATTR amyloidosis experts (including one cardiologist and one neurologist), BresMed, and the Alnylam research team. The survey was reviewed by these parties to improve the clarity and clinical relevance of the topics in relation to the research objectives. The survey had been included as an attachment to the IRB submission.

Patients completing the online survey reviewed and agreed to an informed consent statement prior to completing the survey.

At the end of the survey, patients were asked if they wished to participate in a future in depth interview. A sufficient number of patients agreed to participate, so an extension of this study is being undertaken (Part 2 of this research).

The survey received 1,022 'clicks' into the survey. Due to this unexpected high number of responses, discussions occurred between the research team, clinicians and the ASG leadership on the likelihood of dishonest responses based on known baseline characteristics (age, gender for both cohorts). Therefore, the aim the first ethics amendment was to obtain approval for an additional validation step to identify 'honest' responders. This step included BresMed cross-checking survey respondent email addresses with the ASG patient association membership list (Alnylam had no access to participant email addresses).

Part 2 involves qualitative interviews with a subset of patients who completed the online survey and consented to being contacted regarding completing a follow-up in depth interview. During the interviews, patients will be provided with their individual journey map noting key dates, experienced manifestations and HCPs involved in their ATTR amyloidosis diagnosis journey. This would be generated from their survey results and used to probe key historical events and moments to support the semi-structured interview guides. Please see section 3.2 for more information on the methodology for how we intend to develop and conduct the interviews.

## **2.4.2 Recruitment process**

For Part 1, a study invitation and electronic link to the survey was disseminated by ASG leadership to patient members. Specifically, this patient advocacy organization invited adult patients with ATTRv and ATTRwt amyloidosis to participate in the survey through their patient channels (e.g., email, Facebook, newsletter). The ASG also shared the study informational flyer and study link to its network of ATTR amyloidosis-treating healthcare providers (HCPs) via email. If these HCPs decided to share the study information with their ATTR amyloidosis patients under their care, they were asked to carry out the required ethics steps needed within their local clinical practice. General reminder emails developed by BresMed, Alnylam, and the ASG were sent via the ASG to help increase the response rates.

For Part 2, ATTRwt amyloidosis patients who participated in the online interviews and consented to being contacted for participation in qualitative interviews will be contacted via email by BresMed. If investigators wish to expand the sample population for qualitative interviews to gain further insights, ATTRv amyloidosis patients who participated in the online survey and consented to learn more about interviews may be contacted. Alnylam and the HCPs will not be involved in this process.

## **2.4.3 Sample size**

### **Part 1**

ATTRwt and ATTRv amyloidosis have relatively low prevalence in the US. Due to the nature of the patient population and the desire to improve the generalizability of the results, there was no maximum sample size set for the online survey. Anyone meeting the selection criteria during the enrollment period were allowed to participate in the survey. However, the enrollment period was expected to remain open until a minimum of 60 patients were enrolled (~30 patients with ATTRv amyloidosis and ~30 patients with ATTRwt amyloidosis). The survey stayed open until the target sample size was reached, which was dependent on patient interest and eligibility.

### **Part 2**

The objective of the qualitative interview sample size is to reach data saturation, i.e., the point at which no new themes relevant to the research objectives are being communicated by the patient respondents. Data saturation is a status determined by the expert researchers at BresMed. It is anticipated that saturation may be reached after approximately 15 interviews. However, if data saturation is not reached at this point, additional patients may be recruited, totalling up to 25 interviews. The majority of interviews will focus on patients with ATTRwt amyloidosis with cardiomyopathy, if data saturation is reached early, it is likely the wider ATTR population will be invited to interview, including patients with ATTRwt amyloidosis without cardiomyopathy or ATTRv amyloidosis.

#### **2.4.4 Informed consent**

For Part 1, prior to beginning the survey, patients were presented with full and adequate written information related to the study purpose, procedures, objectives, topics, data integrity, privacy protection, and possible risks and benefits of the study. Patients were informed of the voluntary nature of the study and their ability to discontinue participation at any point.

Patient's e-consent was obtained prior to initiating the survey. E-consents are stored on a secure server and maintained by BresMed.

For Part 2, prior to conducting the in-depth interviews, patients will receive a written/e-copy of the informed consent statement. Additionally, the researcher will affirm each patient's consent after reading aloud a consent statement at the beginning of the interview process. The informed consent form will be attached to the ethics submission.

### **3. Methodology**

#### **3.1 Part 1: Survey administration**

The survey was made available for completion using an online platform disseminated by the ASG. The survey included both open and closed questions and was designed to take 30 minutes to complete. Participation is voluntary and participants were offered a \$30 Amazon gift card as compensation for their time.

##### **3.1.1 Survey selection criteria**

The survey contained initial eligibility questions to ensure participants are interested in participating and meet the survey inclusion criteria via the following prompts multiple eligibility questions related to each inclusion parameter.

Only participants who provided their informed consent and met all inclusion criteria were able to proceed to complete the full survey. Those who were not eligible (e.g., do not meet the inclusion criteria) were diverted to the end of the survey where they were thanked for their time and provided with an opportunity to contact the research team in the event of questions.

In order to participate in the survey, patients were required to meet the following inclusion criteria:

- Patients age 18 and over
- Patients with a confirmed diagnosis of ATTRv or ATTRwt amyloidosis
- English language
- Patient resides in the US

## **3.2 Part 2: Interview administration**

### **3.2.1 Interview selection criteria**

Eligible participants of those initially approached via the web-based survey who are willing to participate in the semi-structured interview will be contacted by a BresMed researcher over the telephone or email (depending on the respondent's preference).

The following pre-defined inclusion criteria will be used to avoid the risk of selection bias:

- Men and women aged 18 and over
- Must be able to provide written informed consent
- Must be able to participate in telephone interviews during the study period (most likely during Q1 2022)
- Must have the cognitive and linguistic skills necessary to participate
- Patients with confirmed ATTRv or ATTRwt amyloidosis
- Completed the survey and included information on type of manifestation, age and type of HCP seen for each manifestation

The participants will be given a full written explanation of the study including background, purpose and steps involved in the interview process. Prior to the interview, they will be sent the study informed consent form by e-mail or post. Those who agree to participate will be asked to sign and return the consent form, and a 1- 1.5-hour appointment will be agreed for the interview with a trained BresMed researcher.

Up to 25 patients will be recruited. Due to the small number of patients with ATTR amyloidosis, randomised sampling is not feasible. Therefore, we will make use of purposive sampling with the aim to interview a variety of patients (e.g. in terms of age, age at diagnosis and severity of disease) to allow us to capture a range of experiences of their journey to an ATTR amyloidosis diagnosis. Following initial review of the survey data, this target number is likely feasible.

### **3.2.2 Interview guide design**

The interview guide will be semi-structured to ensure that topics of interest are covered but provide flexibility for the interviewer to probe and explore newly emerging themes, tailoring the questions to the respondent as needed. The topics covered in the interview guide will be based on those identified as particularly important to patients with ATTR amyloidosis based on the survey analysis and discussions between BresMed, the ASG, medical experts and Alnylam Pharmaceuticals. To support patient recall, the BresMed researchers will share individualised patient journey pathways (developed on PowerPoint) mapping the participants journey as reflected from their individual survey results. This will be shared to the participants prior to the interview giving them time to

review it, discuss it with family or caregivers who were supportive during their ATTR amyloidosis diagnosis to reduce recall bias. The journey pathways will be shared with the participants via PowerPoint/PDF and presented during the interview to help structure the interviews.

Prior to the start of the interviews, an internal pilot interview will be conducted with a BresMed researcher not involved in the project to test the structure, clarity and comprehensibility of the patient questions as well as the length of the interview. It is recommended that one external pilot interview with a patient is also conducted and if possible, feedback will be attained from Alnylam's patient panel, a group of patients with ATTR amyloidosis that meet regularly to review such materials and provide improvements based on their experiences of the condition. After each pilot phase, the interview guides may be slightly adapted to further refine the questions and correct any risk of bias. The final interview guides will be reviewed and approved by Alnylam Pharmaceuticals.

### **3.2.3 Interview process**

The in-depth interviews will be semi-structured in nature and designed to take a maximum of one and a half hours. The interview guide will form the basic structure of the interviews. However, researchers may deviate from the guides to explore any interesting responses provided by participants to ensure that the qualitative interviews provide a rich insight into the patients' perspectives. To minimise the burden to the patients, BresMed will aim to be as flexible as possible in scheduling the interviews to not hinder the recruitment process.

All interviews will be recorded upon consent from the participant for transcribing and data analysis purposes. If participants do not consent to be recorded, notes will be taken during the interview by a second BresMed researcher. The transcriptions of the interviews will be available only to BresMed for analysis purposes. Adverse events (AEs) will be handled in compliance with Alnylam Pharmaceutical's internal pharmacovigilance reporting requirements. All personal information will be stored and handled in accordance with the general data protection regulation (GDPR).

## **3.3 Data collection and data storage**

For Part 1, data collected using the online survey platform was downloaded and stored by BresMed on its secure password protected server for data cleaning and analysis. Personal identifiable information collected in the survey (e.g., email address, IP address) was removed by the BresMed team to prepare an anonymized data set to be shared with Alnylam for storage on a secure password protected server.

For Part 2, personal identifiable information will also be removed from the interview transcriptions and assigned a unique respondent code. Only the researchers who are part of the BresMed will have access to anonymized individual responses held in secure folders on the respective servers. The data collected will only be used for the objectives of this study (see section 3.4.1).

Aggregated results will be shared with Alnylam, the ASG and KOLs, and may also be used for publication; however, anonymized individual patient level data will remain with the research teams from Alnylam and BresMed only. Please see section 3.5 for further information on confidentiality and data protection.

### 3.4 Data analysis and reporting

#### 3.4.1 Analysis

##### Part 1 – Survey:

Due to the unanticipated high enrolment in the survey (>1000 responses between November 30 and December 8, 2020) and uncharacteristic patient demographics (as noted by experienced clinicians and members of the ASG) among survey participants in both hATTR amyloidosis and wtATTR amyloidosis patient groups, particularly in the last 5 days of data collection (Figure 1), it was determined that an additional data cleaning step will be required prior to data analysis to identify ‘true’ patients. A rapid acceleration in patient recruitment and notable change in the average age of participants (i.e., namely, younger participants than is typical for either hATTR or wtATTR amyloidosis) starting on the 5th day of recruitment, Friday November 4, 2020 was observed.

[figure not shown]

**Figure 1.** Day-to-day patient enrolment and mean age of participants throughout the survey recruitment period.

To strengthen internal validity, the ASG leadership confirmed each survey subject's patient status as someone living with ATTR amyloidosis before their data was included in the analysis. To accomplish this, BresMed shared the email addresses collected as part of the survey with the ASG leadership; sharing email information from the following two fields of the survey:

1. Emails provided by the participants who consented to be contacted for follow-up in depth interviews
2. Emails provided by the participants who wished to receive the \$30 Amazon gift card as compensation for their time completing the survey

The ASG leadership cross referenced these email addresses with their own patient list and flagged those emails corresponding to patients who are known to the ASG patient organization.

Additionally, patients who completed the survey and chose not to disclose their email address, including those not to receive the compensatory Amazon gift card, will be included considered for the analysis (maximum 44 participants). It is considered reasonable by the researchers to consider these participants as likely to be patients living with ATTR amyloidosis as they did not have a financial incentive to participate in the study and were more likely to have participated for altruistic reasons. Patient demographics and disease characteristics for the subgroups ATTRwt and ATTRv amyloidosis will be summarized. Through the expert opinions of the researchers, it will be determined whether this cohort reflects the disease characteristics of subjects included in previous publications of ATTR amyloidosis. The researchers will determine whether or not to include these patients in the analysis cohort.

Additional criteria for data cleaning purposes may be considered, such as excluding:

- Responses that come from the same IP address, provided that the responses suggest that it is the same person answering twice
- Respondents that have not mentioned at least one sign/symptom, procedure or other diagnosis
- Respondents who provided inconsistent answers" (e.g. the 'faulty age' criterion, those that put ages older than their diagnosis age)

In summary, only data from participants who adhere to the inclusion criteria and are a) on the validated patient lists (i.e., confirmed by the ASG) and potentially (pending data review) b) who completed the survey but did not opt-in to receive financial compensation and did not disclose their email addresses for other reasons will be used for survey data analysis (i.e., analysis group).

The anticipated statistical or thematic analysis for each question within the survey will be shared with Alnylam for approval prior to the survey analysis. Due to the second objective being to evaluate the similarities and differences between the two conditions, the results will be separated

per condition and analyzed separately. Following this analysis, the results from the two conditions will be compared to highlight the similarities and differences.

Descriptive statistical analysis will be performed on the close-ended questions. Central tendency (median, mode) and variation (range, interquartile range) will be calculated when appropriate. Additionally, thematic data analysis will be applied to recognize patterns in the qualitative data obtained.

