| Analysis                                                                   | 
Part 1 – Survey:
 
 
• Only data from those survey participants whom fit the inclusion criteria and 1) the ASG confirms are patients living with ATTR amyloidosis or 2) completed the survey but did not request financial compensation for their time and did not disclose their email address were included in the analysis (See section 3.3)
 
• Descriptive statistical analysis were performed on the closed-ended questions. In addition, thematic analysis will be conducted on the qualitative data generated by open-ended responses
 
 
Part 2 - Interviews:
                                                         |

|                                                                                                                                                                                                                                                                                                                                                                                                                                                                                                           |                                                                                                                                                                                                                 |
|-----------------------------------------------------------------------------------------------------------------------------------------------------------------------------------------------------------------------------------------------------------------------------------------------------------------------------------------------------------------------------------------------------------------------------------------------------------------------------------------------------------|-----------------------------------------------------------------------------------------------------------------------------------------------------------------------------------------------------------------|

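### Respondents who gave an email are analysed only if they are on the ASG patient list, although recruitment also ran through treating HCPs and membership was not required

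*Protocol*

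**What the plan says.** **Recruitment.** Section 2.4.2 describes two routes. The ASG invited patients "through their patient channels (e.g., email, Facebook, newsletter"). In addition, "The ASG also shared the study informational flyer and study link to its network of ATTR amyloidosis-treating healthcare providers (HCPs) via email", and those HCPs could pass the link to patients under their care. The inclusion criteria (Table 1, section 3.1.1) cover age, diagnosis, language and US residence. They do not require ASG membership.

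**Verification.** After more than 1,000 responses with unusual demographics, section 3.4.1 adds a check. Emails from two survey fields (interview contact and gift card) went to the ASG, which "flagged those emails corresponding to patients who are known to the ASG patient organization".

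**Analysis group.** The summary in section 3.4.1 limits the analysis to eligible participants who are (a) "on the validated patient lists (i.e., confirmed by the ASG"), or potentially (b) completers who took no compensation and disclosed no email. Of group (b) the section says that they "will be included considered for the analysis (maximum 44 participants"), pending the researchers' review. The Analysis row of Table 1 treats the same people as settled: those who "completed the survey but did not request financial compensation for their time and did not disclose their email address were included in the analysis".

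**Target population.** Table 1 gives the survey population as US adults with ATTRv or ATTRwt amyloidosis. Section 2.4.3 names "the desire to improve the generalizability of the results" as one reason for setting no maximum sample size.

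**Date.** Section 3.4.1 places the acceleration in enrolment on the 5th day, "Friday November 4, 2020".

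**The concern.** The list used to confirm patients is narrower than the frame used to recruit them. A genuine patient who received the link from a treating HCP, gave an email for the gift card or an interview, and is not on the ASG list falls in neither (a) nor (b). The protocol treats the step as a way to find honest responders, so such a patient is in effect classed with the dishonest ones. The same could happen to someone reached through Facebook who is not on the list, or to a member who used a different address.

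The primary objectives are disease presentation and HCP interactions before diagnosis. Support-group members may plausibly differ from other patients in disease awareness, length of the diagnostic journey and specialists seen. If so, the filter acts on the quantities being described. Having no cap on enrolment does not offset this, because a larger sample passed through the same list keeps the same selection.

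**Working it through.** The protocol states no figure for this loss, so there is none to reproduce. The check sets the rules side by side and then shows what could and could not be sized.

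**1. Who passes the rule in section 3.4.1**
- Email given, on the ASG list: included under (a), whichever route brought the person in.
- No email, no compensation: possibly included under (b), after a group-level review. Demographics and disease characteristics are summarised by disease type and judged against published cohorts.
- Email given, not on the ASG list: in neither group. This includes a person who declined the gift card but left an email for interview contact.

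Further cleaning criteria (same IP address, no manifestation reported, inconsistent ages) may be applied. They can only remove respondents. They cannot bring an unmatched respondent back.

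**2. Weight of the no-email group**
- Share of survey entries: 44 / 1,022 = 4.3% of clicks.
- Against the minimum target: 44 / 60 = 73%.

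The number confirmed by the ASG is not given, so the share of (b) in the final analysis group is unknown. It could be material, which is why the difference between Table 1 and section 3.4.1 matters.

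**3. Loss of genuine patients (assumptions only)**

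Let h be the share of genuine email-giving patients who came through HCPs, and q the share of those whose email is on the ASG list. Then loss = h × (1 − q).
- h = 10%, q = 50%: 0.10 × 0.50 = 5%.
- h = 50%, q = 0%: 0.50 × 1 = 50%.
- q = 100%: loss = 0 for any h.

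**4. Shift in an estimated percentage (assumptions only)**

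Among genuine email-giving patients, shift = h × (1 − q) × gap, where gap is the difference between excluded and retained patients on a feature. Take h = 10-30% and a gap of 10-20 points:
- q = 0%: 0.10 × 10 = 1 point to 0.30 × 20 = 6 points.
- q = 50%: 0.05 × 10 = 0.5 points to 0.15 × 20 = 3 points.
- q = 100%: 0 points.

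The protocol gives none of h, q or the gap.

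**5. The date**

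The survey ran from 30 November to 8 December 2020, which is 9 days. 30 November 2020 was a Monday, so day 5 is Friday 4 December, and 4-8 December are the last 5 days, as section 3.4.1 describes. 4 November 2020 was a Wednesday and precedes both the opening and the ethics approval of 24 November. Days 1-4 are therefore 30 November to 3 December.

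**The case against.** The case for the rule is serious. With suspected fraud in more than 1,000 responses, favouring certainty over coverage is a defensible way to protect internal validity, and the cross-check received ethics approval. Both recruitment routes ran through the ASG, including its own HCP network, so the sample was ASG-centred before any filter. The study is descriptive. All of this stands, and it is why the verified respondents should remain in the primary analysis.

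Several stronger readings are tempting, but the protocol does not support them:
- A reader might infer that all HCP-referred patients who gave an email are lost. Those whose email is on the ASG list are kept.
- A reader might infer that results apply only to ASG-known patients. Up to 44 no-email completers may also be included.
- A reader might infer that the no-email completers enter unchecked. They face a group-level plausibility review and possible cleaning criteria. That is weaker than individual confirmation, but it is a check.
- A reader might infer that the protocol claims generalizability for the filtered results. Section 2.4.3 offers it only as a reason for having no cap.

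It may also be said that sensitivity analyses belong in a statistical analysis plan, which is not at hand. That is fair, and their absence is not the point. The point is the rule that section 3.4.1 itself fixes, which closes the analysis group to unmatched email-givers.

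**Conclusion.** The point holds in a limited form. Recruitment was open to patients outside the ASG. Verification can confirm only those inside it, and respondents who gave an email and are not on the list have no other way in. Apart from the possible no-email completers, the results describe ASG-known patients, which is narrower than the population in Table 1.

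The size cannot be computed. The 1 to 6 points shown for q = 0% should not be read as an estimate of bias: both ranges are assumed and no HCP-referred patient is taken to be on the list. With full overlap the shift is zero. This is a worthwhile, low-cost improvement and does not invalidate the verified set. The wrong month is clerical in itself, but it marks the cut-off for the analysis proposed below.

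**What to change.** 1. Keep the section 3.4.1 analysis group as primary. Reconcile Table 1 (no-email completers included) with section 3.4.1 (pending review).
2. Report the number of eligible completers excluded because their email was not matched, by day of enrolment.
3. Add one secondary sensitivity analysis that also includes unmatched email-givers who enrolled on days 1-4 (30 November to 3 December 2020), after applying the section 3.4.1 cleaning criteria. Enrolment day does not itself depend on the symptoms or providers a respondent reported.
4. State that conclusions apply to ASG-known patients, plus the no-email completers if they are included. Do not rest generalizability on the absence of a cap.
5. Correct the date in section 3.4.1 to Friday 4 December 2020.

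The cost is one extra analysis on data already collected, one table of counts, and some wording. The drawback is that section 3.4.1 describes the unusual demographics as most marked in the last 5 days, not confined to them. The added set may therefore hold some dishonest responders, how many is unknown, and it must stay secondary.
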